### Randomisation

Randomisation will take place after completion of the screening procedure, informed consent statement and baseline questionnaire before the start of the course. Random allocation will be generated automatically by an online computer program so it cannot be influenced by course facilitators or researchers. A blocked randomisation scheme will be used (blocks of two), stratified by depressive symptoms (scores 10-24 versus 25-45) and age (younger than 18 versus 18 or older). These allocation sequences will be unknown to the course facilitators who are pushing the randomization button. Participants will be informed of their allocation by email and will receive a tailored referral if declined. Course participants will also receive a log-in code and homework for the first session.

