### Assessments

Assessments will take place before randomisation (t0), three months later (t1) and three months after t1 (t2). Participants in both groups will receive automated emails with invitations to complete online questionnaires. Subsequent email reminders will be sent five and ten days after the first invitation, if necessary. To encourage response, participants will receive 10 euros' compensation for completing the t1 questionnaire and 10 euros for the t2 questionnaire. If they complete both questionnaires, a 5-euro bonus will be added, totalling 25 euros.

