### Instruments

#### Primary outcome

##### Depressive symptoms

Symptoms of depression will be assessed with the Center for Epidemiological Studies Depression Scale (CES-D) [31,38]. It measures the frequency of 20 depressive symptoms over the past week using 4-point Likert scales. The total score range is 0 to 60, with a higher rating meaning more depressive symptoms. Computerised and paper-and-pencil versions of the CES-D correlate at a very high level [39]. The web-based CES-D has proved a reliable and valid screening instrument in a Dutch adolescent population [32].

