### Sample size

The trial is powered to detect a clinical effect size of *d *= 0.32 or larger in a one-sided test (alpha = .05) at a power of 80% (1-β). The hypothesis is directional, with better outcomes expected for the course group. A total of 242 participants are needed in the study, n = 121 per condition.

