### Statistical analyses

To assess whether the randomisation results in two comparable groups at baseline, and whether differential loss to follow-up later occurs, we will use t-tests, chi-square tests and logistic regression (p < .10). Analyses with regard to effectiveness will be based on the intention-to-treat principle.

Missing data at t1 and t2 will be imputed using the expectation-maximisation (EM) method, as implemented in SPSS Missing Value Analysis. It imputes missing values by maximum likelihood estimation using the observed data in an iterative process [44]. All randomised participants will be included in the analyses in line with their allocation, regardless of how many sessions they complete (intention-to-treat principle).

Since the online GOJD is a group course, some subjects will be participating in the same course group, leading to some amount of clustering. The clustering would violate the assumption of independence of observations and might thus affect standard errors and *P*-values. We will therefore use linear regression models, controlling for data clustering, in analysing post-test (t1) between-group differences on the continuous outcome measures. Robust standard errors and correct *P-*values will be obtained using the first-order Taylor-series linearisation method, as implemented in Stata.

Magnitudes of intervention effects will be estimated using Cohen's *d *[45]. Effect sizes will first be calculated for each condition separately by subtracting the mean post-test score from the mean pre-test score and dividing the result by the standard deviation at pre-test. The effect size of the comparison group will then be subtracted from that of the experimental group. A difference in *d *0.5 would indicate that the experimental group mean is half a standard deviation greater than the control group mean. For Cohen's *d*, an effect size of 0.2 to 0.3 may be regarded as a small effect, around 0.5 as a medium effect and 0.8 to infinity as a large effect.

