To determine effect maintenance at 6 months in the experimental group, we will use the follow-up (t2) assessment data. The number of participants showing reliable, clinically significant change on the CES-D from pre-intervention to post-intervention and follow-up will be calculated using the method of Jacobson and Truax [46]. To find predictors for more or less successful intervention outcomes, we will use regression analyses to study effect modification. The individual standardised change scores (effectsizes; pre- to post-intervention) will serve as the outcome measure, and interaction terms between the treatment dummy and participants' characteristics will be included as predictors, along with their constituent main effects. Predictors for successful and unsuccessful outcomes will be demographic variables such as age, gender and educational attainment and course-related variables such as web-chatting experience and motivation to take part in preventive group interventions [43].

To detect possible dose-response relationships in respondents randomised to the course, we will use a linear model to regress the primary outcome (depressive symptoms) on the number of sessions they attended. Tests will be conducted at alpha = .05 with 95% confidence intervals.

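### The t1 regression names neither the baseline score nor the stratification factors, while the effect size and predictor analysis use change from baseline; one prespecified baseline-adjusted model would be more precise and would align them

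*Protocol article*

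**What the plan says.** All references are to the protocol article.

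- **Effectiveness model** (Statistical analyses): "We will therefore use linear regression models, controlling for data clustering, in analysing post-test (t1) between-group differences on the continuous outcome measures". Robust standard errors come from Taylor linearisation in Stata. No covariate is named, and the model is not called unadjusted.
- **Timing of baseline** (Assessments): "Assessments will take place before randomisation (t0), three months later (t1) and three months after t1 (t2". The baseline questionnaire is therefore complete before allocation.
- **Allocation** (Randomisation): blocks of two, "stratified by depressive symptoms (scores 10-24 versus 25-45) and age (younger than 18 versus 18 or older".
- **Effect size** (Statistical analyses): Cohen's d is the pre-post change in each arm divided by the pre-test standard deviation, and the two arms' values are then subtracted.
- **Predictor analysis** (Statistical analyses): "The individual standardised change scores (effectsizes; pre- to post-intervention) will serve as the outcome measure", with treatment-by-characteristic interaction terms and their main effects as predictors.
- **Baseline comparability** (Statistical analyses): tested at p < .10, with no stated consequence for the model.
- **Sample size**: "A total of 242 participants are needed in the study, n = 121 per condition", for a standardised effect of "0.32 or larger in a one-sided test (alpha = .05") at 80% power. No allowance for clustering, dropout or baseline correlation is mentioned.

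**The concern.** Followed as written, the main test compares t1 scores between arms and makes no use of a baseline measurement that every participant has given. For a continuous symptom score, the baseline value is usually the strongest single predictor of the follow-up value, so leaving it out gives up precision that costs nothing to obtain. The strata are in the same position: they were used to balance the arms but are not mentioned in the analysis.

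The second issue is that the parts do not match. The test is on t1 scores, but the effect size that will be quoted beside it is on change. In any one sample these differ by the baseline difference between arms. A p-value and a d could therefore suggest somewhat different strengths of effect, with no rule for which governs.

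Precision matters here because the sample size has no slack. The article expects clustering within course groups, and its Background section reports relatively high attrition in earlier online group courses. The calculation shows no allowance for either.

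**Working it through.** **Inputs from the article.** d = 0.32, one-sided alpha 0.05, power 80%, 121 per arm (Sample size).

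**Assumptions.** The t0-t1 correlation r is not given, so I take 0.3 to 0.7. The CES-D entry range of 10 to 45 (Sample) may push r down. SDs at t0 and t1 are taken as equal and set to 1.

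**1. Reproduce the stated size, unadjusted.** n per arm = 2(1.645 + 0.842)² / 0.32² = 120.8, so 121 per arm and 242 in total. This matches exactly. Power at 121 per arm = Φ(0.32 × √(121/2) − 1.645) = Φ(2.489 − 1.645) = 0.801.

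**2. Adjust for baseline.** Residual variance becomes 1 − r², so power = Φ(2.489/√(1 − r²) − 1.645).

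| r (assumed) | 1 − r² | Power, one-sided | n per arm for 80% | Detectable d |
|---|---|---|---|---|
| none | 1.00 | 80.1% | 121 | 0.32 |
| 0.3 | 0.91 | 83.3% | 110 | 0.305 |
| 0.4 | 0.84 | 85.8% | 102 | 0.293 |
| 0.5 | 0.75 | 89.1% | 91 | 0.277 |
| 0.6 | 0.64 | 92.9% | 78 | 0.256 |
| 0.7 | 0.51 | 96.7% | 62 | 0.228 |

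**3. Effect of ignoring the strata.** If the CES-D bands are close to a median split (assumption), they explain about 0.637r² of t1 variance. A standard error that ignores them is too wide. The actual one-sided alpha is 1 − Φ(1.645/√(1 − 0.637r²)), which is 0.045, 0.036 and 0.024 at r = 0.3, 0.5 and 0.7. The test is therefore conservative. Under the same assumption the unadjusted test's real power is 81%, 82% and 85%, so part of the gain in step 2 is already secured by the design; at r = 0.5 the rise is from 82% to 89%.

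**4. Gap between test and effect size.** The change-score difference equals the t1 difference corrected by the t0 difference. The standard error of the t0 difference is √(2/121) = 0.13 SD without stratification. With the CES-D strata near a median split it is √(2 × 0.363/121) = 0.08 SD. One standard error is then 0.13/0.32 = 40% or 0.08/0.32, about 24%, of the design effect. HADS anxiety and mastery are not stratified on, so they lie nearer the upper figure.

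**5. Change score against adjusted t1 score.** The variances are 2(1 − r) and 1 − r²: 1.40 against 0.91 at r = 0.3, 1.00 against 0.75 at r = 0.5, and 0.60 against 0.51 at r = 0.7. The change score is less precise throughout this range, and below r = 0.5 it is noisier than the raw t1 score.

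**6. Clustering, for scale.** Assume an intraclass correlation of 0.05 and course groups at the stated maximum of 6, in the course arm only. Variance in that arm rises by 1 + 5 × 0.05 = 1.25, and the average over arms is 1.125. Unadjusted power is Φ(2.489/√1.125 − 1.645), about 76%. Adjustment recovers this loss when 1 − r² = 1/1.125, that is, r of about 0.33.

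**The case against.** The strongest reply is that the article never says the regression is unadjusted. The quoted sentence answers the clustering problem raised just before it, and a condensed article may leave the covariate list to a fuller document. That stands: a reader might infer that baseline has been excluded, and the text does not support that. What remains is that the section is detailed enough to name software routines and to spell out the predictor model term by term, yet gives clustering as the only control in the effectiveness model. The use of t1 scores for the test and change for the effect size is stated text, not silence.

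The reply also holds on these points:

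- Omitting baseline does not bias a randomised comparison, and ignoring the strata makes the test conservative. Type I error is not inflated.
- The stated 242 does not depend on adjustment. It reproduces exactly without it.
- In expectation, the t1 difference, the change difference and the adjusted difference target the same mean difference. They differ in precision and in the realised value.
- A reader might say that regression to the mean undermines the predictor analysis. It can affect the main effects, but the stated target is effect modification. Regression to the mean is expected equally in both randomised arms and so drops out of the interactions. The case there is precision only.
- A reader might infer that the p < .10 tests will select covariates. Nothing says so; the article only leaves it open.
- The size of the gain rests on an assumed correlation and is about 3 points at r = 0.3.

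**Conclusion.** The point holds as a missed gain in precision and a mismatch between test and effect size. It is not an error that invalidates the analysis. Under the article's own inputs, an unadjusted comparison is unbiased and has 80% power before clustering and dropout. Baseline adjustment would raise that to about 83-97% for r between 0.3 and 0.7. The rise is somewhat less if the strata are already doing part of the work. The correlation is an assumption, and the entry range may place it toward the lower end. The mismatch does not depend on r: one standard error of chance baseline difference is roughly 24-40% of the design effect, the lower figure assuming CES-D strata near a median split. The change should be made before the data are seen, but the trial does not depend on it.

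**What to change.** - **Model.** For each continuous outcome (CES-D, HADS anxiety, mastery), prespecify t1 score on allocation, the continuous baseline value of that outcome and the stratification factors. Use cluster-robust standard errors by course group, with each waiting-list participant as a separate cluster. For CES-D, the age stratum is the factor that matters; the CES-D stratum adds little once continuous CES-D is included.
- **Effect size.** Derive it from the adjusted difference divided by the baseline SD, so that it matches the test.
- **Effect modification.** Use t1 CES-D as the outcome with baseline CES-D as a covariate, and keep the planned interaction terms and their main effects.
- **Baseline tests.** State that the p < .10 comparisons are descriptive and do not choose covariates.

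The cost is a few sentences, with no new data collection. There is one small downside. The planned single EM imputation may place imputed t1 values close to the regression on baseline. If it adds no residual error (the article does not say), an adjusted model will understate residual variance, so the imputation step should be checked when the model is fixed.

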#### Secondary outcomes

##### Anxiety symptoms

The anxiety subscale of the Hospital Anxiety and Depression Scale (HADS) [40] will be used to assess anxiety symptoms. The Dutch version of the HADS has been validated [41]. The anxiety subscale consists of seven items measuring anxiety symptoms on a 4-point Likert scale, with a score range of 0 to 21, and a higher rating indicating a higher state of anxiety.

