#### Perceived control

The Dutch version of the 5-item Mastery Scale will be used to assess perceived control [42]. The concept of mastery refers to beliefs about one's own ability to control one's environment. Responses are rated on a 5-point Likert scale, with a total score range of 5 to 25; a higher score indicates a greater sense of mastery. The Mastery Scale has good psychometric properties [42].

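### The Cohen's d rule makes benefit on mastery negative, is interpreted wrongly in the text, and, if each arm is scaled by its own SD, adds avoidable noise

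*Protocol article*

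**What the plan says.** All references are to the protocol article, Methods.

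- **Per-arm step (Statistical analyses).** "Effect sizes will first be calculated for each condition separately by subtracting the mean post-test score from the mean pre-test score and dividing the result". The divisor is the pre-test SD; no pooled or common SD is named.
- **Between-arm step (same section).** "The effect size of the comparison group will then be subtracted from that of the experimental group".
- **Interpretation (same section).** A difference in d of 0.5 "would indicate that the experimental group mean is half a standard deviation greater than the control group mean".
- **Direction of the scales.** For CES-D: "The total score range is 0 to 60, with a higher rating meaning more depressive symptoms". For HADS anxiety: "a higher rating indicating a higher state of anxiety". For mastery: "a higher score indicates a greater sense of mastery".

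The effect-size rule makes no exception by outcome. The test of effectiveness is separate: a linear regression on t1 scores with standard errors robust to clustering.

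**The concern.** The rule is stated in full, so this is not detail that a condensed article leaves to a fuller plan. Followed literally, it has three defects.

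1. **Sign.** Pre minus post is positive when a score falls. That marks improvement on two of the three scales and deterioration on the third.
2. **Meaning.** The interpretive sentence describes a gap between two group means, with the course mean higher. The rule produces a gap between two standardised changes, and on the primary outcome a higher mean is worse.
3. **Unit.** If each change is divided by its own arm's SD, the rule subtracts two quantities measured in different units.

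At stake is the reported size of effect. Cohen's d is the only measure the section names for the magnitude of intervention effects, and it is to be read against small, medium and large labels.

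**Working it through.** **The plan's own figure.** d = 0.32, one-sided alpha 0.05 and 80% power give 121 per arm and 242 in total (power at 121 per arm: 0.801). This agrees with the Sample size section and does not depend on the effect-size rule.

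**The rule as a formula**, with E the course arm and C the control arm:

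d = (pre_E − post_E)/SD_E − (pre_C − post_C)/SD_C

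The article gives no means, SDs or changes, so the values below are assumptions chosen for illustration.

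**(a) Sign on mastery.** Course 14 to 16, control 14 to 14.5, SD 4 in both arms:

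d = (14 − 16)/4 − (14 − 14.5)/4 = −0.5 + 0.125 = −0.375

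The course arm gained more mastery, yet d is negative. The sign follows from the formula whatever values are chosen.

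**(b) Interpretation on CES-D.** SD 8 in both arms.

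- Course 28 to 20, control 28 to 24: d = 8/8 − 4/8 = +0.5. The course post-test mean is (20 − 24)/8 = −0.5 SD from control, so it is half an SD lower, not greater.
- Course 30 to 22, control 26 to 22: d = 8/8 − 4/8 = +0.5 again, although the post-test means are identical.

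**(c) Own-arm scaling.** With the same raw change in both arms:

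d = change × (1/SD_E − 1/SD_C)

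This is zero only if the change is zero or the two sample SDs match.

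- Change 8, SDs 8 (course) and 9 (control): 1.000 − 0.889 = +0.11.
- Change 8, SDs 9 and 8: −0.11.
- The sign can flip. Course change 8 with SD 10 and control change 7 with SD 8 give 0.800 − 0.875 = −0.075. With the pooled SD √((100 + 64)/2) = 9.06, d = 1/9.06 = +0.11.

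**How large is (c) by chance?** With normal scores, equal true SDs and 121 per arm, the ratio of sample SDs lies between about 0.84 and 1.20 in 95% of trials. If k is the common improvement in true SDs, the SD of the artefact is about k/√(n − 1) = k/10.95. Simulation gives:

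| Common improvement | k/10.95 | Normal scores | Scores truncated to 10–45, stratified blocks of two |
|---|---|---|---|
| 0.3 SD | 0.027 | 0.029 | 0.022 |
| 0.5 SD | 0.046 | 0.047 | 0.036 |
| 1.0 SD | 0.091 | 0.092 | 0.072 |

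The normal-score column assumes a pre-post correlation of 0.5. The last column assumes a normal distribution with mean 28 and SD 10 before truncation, and 25% of participants under 18. The mean artefact is about zero.

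For comparison, when the true difference is zero, the SD of d with a pooled SD is about 0.13. Own-arm scaling raises it to 0.137 at a common improvement of 0.5 SD and to 0.159 at 1 SD (normal scores).

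**The case against.** The best reply is that d is descriptive. Effectiveness is tested by the regression on t1 scores, so nothing here alters a p-value, the sample size or the primary conclusion. That stands.

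It is also fair that the article does not spell out own-arm SDs: it says "dividing the result by the standard deviation at pre-test". Since the calculation is done for each condition separately and no common SD is named, own-arm scaling is the natural reading, but part (c) depends on it. Parts (a) and (b) do not.

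On mastery, one can say that each scale's direction is defined, so a careful reader can decode a negative d. That softens the consequence. It does not remove the inconsistency of one rule giving benefit opposite signs across outcomes. The interpretive sentence could be rescued for CES-D by taking group mean to be mean improvement, but it does not say that, and the reading still fails for mastery.

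Three stronger readings are tempting and are not supported:

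- **That the rule biases d.** Randomisation makes the two SDs equal in expectation, so the artefact averages about zero.
- **That it typically shifts d by an amount comparable with the planned 0.32.** Shifts of about ±0.15 (5–95% range) require both arms, including an untreated waiting list, to improve by a full SD with normal scores. Nor does the article say that the observed d will be compared with 0.32, or call d its headline result.
- **That scaling by a baseline SD is itself wrong because entry is limited to CES-D 10–45.** Baseline-SD scaling is a legitimate, pre-stated choice, and a pooled baseline SD carries the same restriction.

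**Conclusion.** The point holds as a defect in how the magnitude of effect is defined and explained, not in the test of effectiveness. The sign on mastery and the interpretive sentence are wrong on the article's own wording and need no assumption. Own-arm scaling is a lesser matter and rests on the natural but unstated reading of the rule. It adds noise with an SD of about 0.02 to 0.05 for a common improvement of 0.3 to 0.5 SD, and 0.07 to 0.09 for 1 SD, at 121 per arm under the assumed distributions. That is modest beside the ordinary sampling SD of about 0.13, but it is avoidable. The correction is worth making because it costs almost nothing.

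**What to change.** 1. Divide one between-arm difference by one pooled baseline SD of both arms. The difference may be that in mean change or the t1 difference from the primary regression; state which.
2. Report it with a cluster-robust 95% CI.
3. Sign it so that positive favours the course on every scale. For change scores this is pre minus post on CES-D and HADS anxiety, and post minus pre on mastery.
4. Reword the interpretive sentence: 0.5 means that the course group improved by half a pooled baseline SD more than the control group. If the unadjusted t1 difference is the numerator, say instead that the course group ended half a pooled baseline SD better.

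The cost is a few sentences of text. No new data are needed, and the sample size and the regression stay as planned.

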### Sample

The sample is to consist of 242 young people aged 16-25 with mild to moderate depressive symptoms. The inclusion criteria are as follow: age 16 to 25, informed consent (including parental consent if aged 16 or 17) and a CES-D depression score from 10 to 45. The CES-D cut-off score for clinical depression is 16 [31] for adults, and for adolescents it is either 22 [32] or 24 [33]. For subclinical depression, no CES-D cut-off scores have been determined, but we have set the lower limit at 10 for this study. Applicants will be excluded if there are indications of suicidal ideation with intent and plan as assessed with the MINI-International Neuropsychiatric Interview (MINI-Plus) [34,35]. MINI-Plus assessment is mandatory for individuals with CES-D scores higher than 24; the MINI-Plus will be administered online in the chatroom.

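### The effect-modification analysis uses change scores with no stated baseline CES-D term, so its interaction tests are valid but less precise than the collected data allow

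*Protocol article*

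**What the plan says.** The Statistical analyses section of the article sets out the predictor analysis in some detail. Its purpose is effect modification: "we will use regression analyses to study effect modification". The outcome is fixed: "The individual standardised change scores (effectsizes; pre- to post-intervention) will serve as the outcome measure". So are the regressors: "interaction terms between the treatment dummy and participants' characteristics will be included as predictors, along with their constituent main effects". The candidate characteristics are given as examples: "demographic variables such as age, gender and educational attainment" and "course-related variables such as web-chatting experience and motivation to take part in preventive group interventions".

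Baseline CES-D is not stated as a covariate in this model, and baseline severity is not among the examples. The Randomisation section makes severity a design variable, since allocation is "stratified by depressive symptoms (scores 10-24 versus 25-45) and age (younger than 18 versus 18 or older". The Background and Discussion name the identification of predictors of positive outcome as a secondary aim.

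**The concern.** A pre-post change score carries the baseline score with a fixed coefficient of one. Unless t1 really moves one-for-one with baseline, that adds variation to the outcome which a baseline covariate would remove. The trial is sized for a main effect, so its interaction tests are weak from the start, and avoidable residual variance weakens them further.

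There is a second, smaller matter. If depression severity itself modifies the effect of the course, and a characteristic such as age or motivation is correlated with severity, that characteristic's interaction with treatment can pick up the severity effect unless severity-by-treatment is also in the model.

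At stake are the power and the interpretation of a declared secondary analysis. The primary comparison is not involved.

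**Working it through.** **Inputs from the article.** Total 242, 121 per arm; d = 0.32; one-sided alpha .05 and 80% power for the primary comparison (Sample size); alpha .05 with 95% confidence intervals for tests (Statistical analyses).

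**Inputs assumed.** The pre-post correlation r (.3 to .7), equal SDs at t0 and t1 unless stated otherwise, a 50/50 binary modifier for the detectable-effect figures, and no clustering. The article gives none of these.

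**1. The plan's own figure.** n per arm = 2 × (1.645 + 0.842)² / 0.32² = 12.37 / 0.1024 ≈ 120.8, so 121 per arm and 242 in total. The stated figure reproduces, and nothing below changes it.

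**2. Residual variance.** In units of the baseline variance, the change score has variance 2(1 − r) and the baseline-adjusted t1 score has 1 − r². The ratio is (1 − r²) / [2(1 − r)] = (1 + r)/2.

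**3. Smallest detectable interaction** (80% power, two-sided .05): 2.80 × 4 × SD / √242, in baseline SD units.

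| r | variance, change score | variance, adjusted | ratio | detectable, change score | detectable, adjusted |
|---|---|---|---|---|---|
| .3 | 1.40 | 0.91 | 0.65 | 0.85 | 0.69 |
| .5 | 1.00 | 0.75 | 0.75 | 0.72 | 0.62 |
| .7 | 0.60 | 0.51 | 0.85 | 0.56 | 0.51 |

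At r = .5, an adjusted analysis of 242 × 0.75 ≈ 182 participants would match the change-score analysis of all 242.

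**4. Unequal SDs.** With t0 SD s0 and t1 SD s1, the change-score variance minus the adjusted variance is (s0² + s1² − 2r·s0·s1) − s1²(1 − r²) = (s0 − r·s1)². This is never negative, but the gain shrinks if s1 exceeds s0. That is plausible here, because entry requires "a CES-D depression score from 10 to 45" and so restricts the baseline range. If s1 = 1.2·s0 and r = .5, the variances are 1 + 1.44 − 1.2 = 1.24 and 1.44 × 0.75 = 1.08, a ratio of 0.87 in place of 0.75.

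**5. Validity of the interaction.** Simulations had N = 242 and 5,000 runs each, with a binary characteristic whose baseline mean differs by 0.3 or 0.5 SD and which has no true link with response. At r = .4 to .7 the interaction was rejected in 4.7% to 5.7% of runs with the change score. There is no inflation.

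**6. Severity as a true modifier.** In the same set-up at r = .5, the treatment effect was made to vary by 0.2 or 0.3 SD per SD of baseline. The characteristic's interaction was then rejected in 5.9% to 8.5% of runs with the change score, in 6.4% to 10.9% with baseline added alone, and in 4.7% to 5.7% once treatment-by-baseline was also in the model.

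**7. Price of that extra term.** For a standardised continuous characteristic at r = .5, the interaction's standard error falls from about 0.129 with the change score to 0.113 with baseline added. With treatment-by-baseline also added it is 0.115 to 0.123, for a characteristic correlated .2 to .4 with baseline. At r = .7 and correlation .4 the gain is used up. If the characteristic relates to t1 only through baseline, the two residual SDs to compare are √(0.51 / (1 − 0.16)) = 0.78 for the full model and √(0.60 − 0.16 × 0.09) = 0.77 for the change score.

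**The case against.** The change score is a defensible outcome. It gives a valid test of each interaction, and it matches the article's own definition of effect size, which subtracts post-test from pre-test and divides by the pre-test SD. Both points stand; what remains against it is precision.

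A reader might infer something stronger: that regression to the mean will make the plan declare false predictors, and that baseline adjustment would cure this. The documents do not support that.

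- The stated aim is effect modification, which is read from the interactions, and these hold their nominal level. The characteristics' main effects enter as constituents of those interactions. The article does call all these terms predictors, so reporting a main effect as a finding is possible, but it is not stated.
- Neither model is neutral for the main effect of a non-randomised trait. Take r = .5, 0/1 treatment coding and a trait correlated .2, .3 or .4 with baseline. If the trait is unrelated to t1 given baseline, the change-score main effect is rejected about 20%, 38% and 60% of the time and the adjusted one about 5%. If the trait differs equally at both times, the change score rejects about 5% and the adjusted model about 27%, 53% and 83%. Which result is false depends on whether the question concerns change or t1 given baseline.

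A reader might also infer that severity was left out as a modifier. Both lists of characteristics are open, and the article condenses a fuller plan, so severity is unnamed but not excluded. Naming it is a suggestion; its absence is no error.

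**Conclusion.** The point holds as one of efficiency. The stated model discards information that the trial collects before randomisation and uses to stratify. Under equal SDs, 15% to 35% of the change-score residual variance is removable for r from .7 down to .3, and 25% at r = .5. At r = .5 the detectable interaction falls from 0.72 to 0.62 baseline SD. The gain is smaller if the t1 SD exceeds the baseline SD, and the figures ignore clustering within course groups.

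Crediting a severity effect to a correlated characteristic is a modest risk. It arises only if severity truly modifies the effect and the characteristic correlates with it.

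The interactions are valid as planned. The primary analysis and the sample size are untouched. This is a worthwhile improvement to a secondary analysis and does not correct an invalid one.

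**What to change.** Replace the change-score outcome in the predictor analysis with t1 CES-D. Regress it on continuous baseline CES-D, treatment, the characteristic and treatment-by-characteristic, using the same cluster-robust standard errors as the primary analysis. If standardised units are wanted, divide by one baseline SD pooled over the arms.

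Add treatment-by-baseline CES-D to the model and name severity as a modifier. State that this term costs some precision when the characteristic is correlated with baseline.

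Say that only the interactions will be reported as predictors of intervention success, and that main effects of the characteristics will not be presented as such.

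The cost is a few sentences of analysis wording. It needs no new data, because baseline CES-D is already required for stratification and for the change score itself, and no participants are lost.
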